### Selection of acupuncture points

Previous clinical trials have confirmed that electroacupuncture at the Zusanli and Guanyuan acupoints can improve clinical outcomes in patients with S-AGI, possibly by improving gastrointestinal motility. A prospective controlled trial involving 60 sepsis patients showed that electroacupuncture at the Zusanli and Guanyuan acupoints improved clinical efficacy, potentially through mechanisms related to immune regulation (10). Another randomized controlled trial involving 55 sepsis patients found that abdominal acupuncture could improve symptoms of S-AGI by reducing gastrin and gastric secretions, thereby promoting gastrointestinal function recovery (17). Based on these findings, we chose the Zusanli and Guanyuan acupoints as the target acupuncture points for this research protocol.

### Methods of acupuncture in the EA group

Patients will be placed in a supine position for acupuncture treatment. Sterile, disposable stainless steel acupuncture needles (0.25 mm or 0.35 mm gauge, Hanyi Medical Instrument Co., Ltd., Beijing) will be gently inserted at the designated acupuncture points. For ST36, needles will be inserted perpendicularly to a depth of approximately 10–30 mm from the skin surface. For RN4, needles will be inserted obliquely to a depth of 10–30 mm at a 30-degree angle toward the patient’s feet, without lifting or thrusting. An electric stimulator (G6805-A EA apparatus; Huayi Industrial Co., Ltd., Shanghai, China) will be connected to the needle handles at the bilateral ST36 and RN4 points, delivering a continuous 5-Hz wave. The current intensity will be increased to a maximum level ranging from 1 to 5 mA, ensuring the absence of localized muscle twitching or any discomfort that might cause the patient to frown. The needles will be retained for 30 min. All acupuncturists will be licensed, have more than 3 years of clinical experience, and receive training on the specific study protocol.

Patients in the EA group will receive acupuncture treatment twice daily for 7 days. The first session will be conducted between 08:30 and 12:00, and the second session will be conducted between 14:00 and 17:00. A total of 14 acupuncture sessions will be conducted.

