### Methods of acupuncture in the control group

Patients in the control group will receive only the conventional treatment described above, without acupuncture, for 7 days after randomization.

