#### Secondary outcomes

Secondary outcomes consist mainly of 16 indicators. It includes clinical and prognostic indicators (key secondary outcomes) and biochemical indicators (exploratory outcomes).

Clinical indicators include the following: (1) Average classification of the AGI grade, (2) gastric retention volume within 1 day, (3) abdominal circumference, (4) abdominal pressure, (5) frequency of bowel sounds, (6) number of days tolerating the daily feeding target, (7) proportion of patients receiving erythromycin and/or metoclopramide for feeding intolerance management, and (8) proportion of patients receiving one or more rectal laxatives for constipation management.

Biochemical indicators include the following: (1) Plasma concentration of motilin, (2) plasma concentration of gastrin, and (3) plasma concentration of prealbumin.

Prognostic indicators include the following: (1) Incidence of S-persistent inflammation, immunosuppression, and catabolism syndrome (PICS), (2) duration of invasive mechanical ventilation in days, (3) ICU length of stay in days, (4) mortality rate at day 7, and (5) mortality rate at day 28.

To assess gastrointestinal function, the AGI grade will be used (4). The AGI grade is widely used to evaluate gastrointestinal injury in patients with acute critical illness (4, 18). Evidence has shown that the AGI grading system is useful for determining the severity of gastrointestinal dysfunction/failure in sepsis (19). The specific criteria for AGI grading are provided in Supplementary File S1.

At baseline and on days 4, 8, and 10, AGI grading will be assessed, and gastric retention volume, abdominal circumference, abdominal pressure, and frequency of abdominal bowel sounds will be measured. The specific measurement procedures for these clinical indicators are detailed in Supplementary File S1. We will also record the gastric retention volume over the previous 24 h, the actual caloric intake from enteral nutrition, and any special treatments related to S-AGI, including the use of erythromycin and/or metoclopramide for feeding intolerance management or the use of one or more rectal laxatives for constipation management. In addition, we will collect venous blood samples from patients at baseline and on days 4, 8, and 10 to measure the plasma concentration of motilin and gastrin, which serve as indicators of gastrointestinal motility.

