In open-label clinical studies, there is a high risk of selection, performance, and measurement bias. To minimize these biases, we will implement the following measures. First, to prevent selection bias, inclusion and exclusion criteria will be defined clearly to ensure baseline consistency among participants and reduce potential effects on outcomes. Randomization sequences will remain concealed until participants are confirmed eligible and enrolled. Second, to minimize performance bias, standardized intervention protocols and detailed manuals will be used in operations. Researchers will receive training from the project leader to ensure consistent implementation and assessment. Third, to mitigate measurement bias, outcome assessors and statisticians will be blinded to treatment assignments and data, respectively, until the analysis is complete. We will use an intention-to-treat approach to include data from all participants regardless of study completion, and we will report the reasons for, as well as the number of, missing data in each group.

This study will be the first large-sample randomized controlled trial to evaluate the efficacy of electroacupuncture in preventing S-AGI in patients with sepsis undergoing mechanical ventilation. We will assess the effects of electroacupuncture and compare the difference between the electroacupuncture and standard care groups in an adequately powered trial.

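### Whichever blinding statement governs, the S-AGI assessor may be able to infer the arm: only EA patients are needled, and the listed bias measures do not address this

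*Protocol article*

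**What the plan says.** **Needling.** Under Methods of acupuncture in the EA group, needles go in at bilateral ST36 and at RN4: "For RN4, needles will be inserted obliquely to a depth of 10–30 mm at a 30-degree angle". The schedule is: "Patients in the EA group will receive acupuncture treatment twice daily for 7 days", with a morning session between 08:30 and 12:00 and an afternoon session between 14:00 and 17:00, 14 sessions in all. In the other arm: "Patients in the control group will receive only the conventional treatment described above, without acupuncture". There is no sham.

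**Assessment.** The Secondary outcomes section says what is done on each assessment day: "AGI grading will be assessed, and gastric retention volume, abdominal circumference, abdominal pressure, and frequency of abdominal bowel sounds will be measured". Those days are baseline, then 4, 8 and 10. Quality control asks for one person to evaluate gastrointestinal function throughout the trial. The primary outcome is new gastrointestinal symptoms with an AGI grade of 1 to 4, by day 10.

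**Blinding.** The Abstract and the Randomization section limit blinding to blood test assessors and statisticians, and Study design calls the trial open-label. The Discussion lists measures against bias and says: "to mitigate measurement bias, outcome assessors and statisticians will be blinded to treatment assignments and data, respectively, until the analysis is complete". It also argues that patients are sedated, so the lack of a sham will leave outcome assessments unaffected.

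**The concern.** The primary outcome turns on a bedside judgement, namely whether a patient has crossed from no AGI to grade 1, and one person is to make that judgement for the whole trial. If that person knows or suspects the arm, the threshold can shift in one direction. With a single rater, no averaging over raters dilutes the shift.

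The Discussion presents assessor blinding as the protection against this. Two things weaken it. First, the Abstract and Randomization section say the bedside assessor is not blinded. Second, even if the contradiction is settled in favour of blinding, the assessor examines patients of whom one arm only has been needled, and one of the three follow-up assessments falls on a treatment day. At stake is whether a difference in S-AGI incidence can be read as an effect of EA and not of its rating.

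**Working it through.** **1. The blinding statements side by side.**

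| Place in the article | Status of the bedside S-AGI assessor |
|---|---|
| Abstract, Methods | Not among those blinded |
| Randomization | Not among those blinded |
| Study design | Trial is open-label |
| Discussion, measures against bias | Outcome assessors blinded until the analysis is complete |

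If the first three govern, the primary outcome is graded openly. If the last governs, the question is whether that blinding can hold at the bedside.

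**2. What the assessor could meet.** The acupuncture row of Table 1 shows no day marks as extracted, so I assume that sessions run from day 1 to day 7.
- Sessions before day 4: 2 per day × 3 days = 6.
- Sessions by the end of day 7: 2 × 7 = 14.
- Day 4 lies within treatment. Day 8 is one day after the last session day, and day 10 is three days after it.
- Session hours are fixed for both halves of the day. The article gives no assessment hour, so on day 4 an assessment could coincide with a session or follow it closely, in one arm only.

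The article does not say where RN4 lies. An abdominal site is assumed here. It fits the section on selection of points, which cites a trial in which "abdominal acupuncture could improve symptoms of S-AGI".

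**3. The sham argument.** Sedation can limit a patient's expectation or report. It does not bear on what an examiner sees or hears at the bedside, so the premise does not carry the conclusion.

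**4. The plan's own figures.** For 70% versus 50%, two-sided α = 0.05 and power 0.80, with pooled variance under the null:

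n = [1.960·√(2·0.60·0.40) + 0.842·√(0.21 + 0.25)]² / 0.20² = 93 per group (stated: 94).

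The same formula gives 163 for 70% versus 55% and 356 for 70% versus 60%, both as stated. The sample size is not in dispute.

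**5. Illustration of rater bias.** Assume EA has no effect: true S-AGI is 70% in both arms, with 100 per arm. The assessor fails to call a share m of true cases in the EA arm, so the observed EA rate is p = 0.70·(1 − m). With d = 0.70 − p and p̄ = (0.70 + p)/2:

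SE₀ = √(2·p̄·(1 − p̄)/100), SE₁ = √((0.21 + p·(1 − p))/100),

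P(significant, favouring EA) = 1 − Φ((1.960·SE₀ − d)/SE₁).

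| m (assumed) | p | d | SE₀ | SE₁ | P |
|---|---|---|---|---|---|
| 0% | 0.700 | 0 | 0.0648 | 0.0648 | 2.5% |
| 2% | 0.686 | 0.014 | 0.0652 | 0.0652 | 4.0% |
| 5% | 0.665 | 0.035 | 0.0658 | 0.0658 | 7.6% |
| 10% | 0.630 | 0.070 | 0.0668 | 0.0666 | 18.0% |
| 15% | 0.595 | 0.105 | 0.0676 | 0.0672 | 34.2% |
| 20% | 0.560 | 0.140 | 0.0683 | 0.0676 | 53.6% |

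The values of m are not from the article. The table shows how sensitive the primary test is to one-sided rating. It does not estimate how much of that needle marks would cause.

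**The case against.** **Procedures may exist elsewhere.** The measurement procedures are in Supplementary File S1, which is not shown, and the Discussion mentions detailed manuals. Site covering and the hour of an examination are details that an article may leave to such documents. This stands: one cannot say that the trial has no masking or timing rule. One can say that the Discussion enumerates its measures against bias and that neither is among them.

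**There may be no blinding to break.** Under the Abstract and Randomization section the assessor is simply open. This also stands, and the contradiction is the firmest part of the point. It does not remove the concern, because an open assessor is at least as exposed to rating bias.

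**Visibility is not shown.** A reader might infer that the assessor will see the arm and that the examination itself destroys the blinding. The documents do not support that. Needles are fine ("0.25 mm or 0.35 mm gauge") and are not lifted or thrust, nothing says that marks persist, and on the assumed schedule two of the three follow-up assessments come after treatment. The Safety assessment section names haematoma and bleeding only to say how such events would be attributed, alongside a statement that risk is minimal. It does not predict them. Nor does the article say that control patients' abdomens are otherwise unmarked, or that grading and abdominal measurement are a single examination. They share days.

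**The figures are not specific.** The shading rates are assumed and are applied to every EA case whatever its grade. If incidence counts a positive grade on any assessment day, a case is lost only when it is missed each time it is present. Reading the 54% as the effect of visible needle sites would be wrong.

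**Conclusion.** The point holds in a limited form. The article contradicts itself on whether the S-AGI assessor is blinded. If blinding is intended, the assessor may be able to infer the arm, most plausibly on day 4, and the bias measures listed in the article do not address that route. The Discussion's sentence on the missing sham is not supported by the reason given for it.

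The direction of concern is towards EA, because a rater who expects benefit would under-call in that arm. The size is unknown. Under the assumed shading rates of 5%, 10% and 20%, the chance of a false finding for EA is about 7.6%, 18% and 54%, against 2.5%; these figures illustrate rater bias in general. The conclusion rests on sessions running from day 1 to day 7, on RN4 being an abdominal site, and on what the article itself states, since Supplementary File S1 was not available. This is a cheap improvement worth making. It is not a demonstrated failure of blinding.

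**What to change.** 1. Reconcile the Abstract and Randomization section with the Discussion so that all say that the assessor who grades S-AGI is blinded to allocation.
2. In the intervention and outcome sections, state that before each day-4, day-8 and day-10 assessment existing bedside staff cover RN4 and both ST36 sites with identical opaque dressings in both arms, left on until the assessment ends.
3. Hold the day-4 assessment before that day's first EA session (before 08:30), at the same hour in both arms, and keep the assessor away from sessions.
4. Correct the Discussion sentence on the sham: sedation bears on the patient, and the protection against rater bias is the masking in items 1 to 3.
5. Optionally, have the assessor record a guess of the arm on day 10.

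If Supplementary File S1 already contains such rules, a sentence in the article pointing to them would do for items 2 and 3.

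**Cost.** Three small dressings on three days per patient, a few minutes of nursing time and a fixed assessment hour. There are no extra visits, and neither the EA sessions nor the sample size changes.

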### Methods of acupuncture in the control group

Patients in the control group will receive only the conventional treatment described above, without acupuncture, for 7 days after randomization.

### Relevant concomitant care and interventions

In principle, within 7 days after randomization, all participants will not receive any other traditional Chinese medicine therapies, such as herbal medicine or moxibustion, except for the electroacupuncture specified in the protocol for the intervention group. Participants may receive other traditional Chinese medicine treatments prior to randomization, but not during the first 7 days following randomization. Receipt of any important interventions outside the study protocol should be documented in detail on the case record form.

### Outcomes

#### Primary outcome

The primary outcome is the 10-day incidence rate of S-AGI.

The occurrence of S-AGI is defined as the development of gastrointestinal symptoms in a patient who had no symptoms at baseline, with an AGI grade of 1 to 4 at the time of assessment.

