## Introduction

### Background and rationale

Sepsis is defined as life-threatening organ dysfunction caused by a dysregulated host response to infection (1). Sepsis and septic shock are major causes of global morbidity and mortality (2), and data from high-income countries indicate that the annual incidence of sepsis is 31.5 million, with 19.4 million cases of severe sepsis contributing to 5.3 million potential deaths annually. Hospital mortality rates are reported to be 17% for sepsis and 26% for severe sepsis (3). There are limited comparable data from low- and middle-income countries, where the burden of sepsis may be even greater. Septic acute gastrointestinal injury (S-AGI) plays a key role in the initiation and progression of sepsis. Early-stage sepsis may cause intestinal barrier dysfunction, gastrointestinal motility disorder, and translocation of intestinal flora, leading to multiple organ dysfunction syndrome (MODS). Once MODS is initiated, it contributes to the development and worsening of gastrointestinal dysfunction, leading to increased hospitalization and mortality rates (4). According to existing literature, patients who were provided with preventive treatment for acute gastrointestinal injury (AGI) showed a significant increase in nutrient solution intake and a notable decrease in the duration of invasive mechanical ventilation compared to those who did not receive any preventive measures (5).

Treatments for S-AGI include early enteral nutrition, gastric motility drugs, acid inhibitors, and antimicrobial agents, which aim to protect the gastrointestinal mucosa, increase gastrointestinal motility, and improve intestinal flora (4, 6, 7). Despite the availability and application of S-AGI treatments, the case fatality rate for sepsis-3 is estimated to exceed 30%, corresponding to 700,437 deaths in China (8). Therefore, there is an urgent need to explore novel and supplemental treatments to improve clinical outcomes.

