Growing evidence suggests that acupuncture alone, or in combination with Western medicine, can improve the clinical prognosis of S-AGI, including significant reductions in 28-day mortality and improvements in AGI grade and gastrointestinal function. A retrospective propensity score-matched cohort study conducted by our team evaluating the effects of electroacupuncture (EA) at “Zusanli” (ST36) and “Guanyuan” (RN4) on S-AGI demonstrated a 54% reduction in 28-day mortality among patients who received EA (9). Furthermore, in our recent randomized controlled trial (RCT), electroacupuncture combined with standard treatment improved clinical outcomes by regulating the immune system compared to standard treatment alone (10). Meng et al. conducted an RCT and reported that patients with S-AGI exhibited significant improvements in AGI grade and gastrointestinal function when acupuncture was used as an adjunctive therapy (11). However, findings regarding its impact on mortality have been inconsistent. Meng et al. found that the use of acupuncture as an adjuvant therapy decreased 28-day mortality in patients with S-AGI compared to standard treatment alone (11). However, another RCT reported no significant effect on mortality (12). Therefore, studies with a larger sample size are needed to clarify the effects of acupuncture on both gastrointestinal function and mortality in patients with sepsis.

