### Sample size

A parallel-design, randomized controlled trial methodology will be employed in the trial, with the primary outcome measure being the incidence of S-AGI. Based on clinical observations, the estimated incidence of S-AGI in the conventional treatment group is 70%. It is anticipated that electroacupuncture can potentially reduce the occurrence rate of S-AGI to 50%. With a significance level (*α*) of 0.05 and a power of 0.8, the sample size calculation yielded 94 participants per group. To account for potential loss to follow-up, we plan to include a total of 200 sepsis patients, with 100 patients allocated to each group. To account for uncertainties and maintain adequate power if the effect size is smaller than expected, sample sizes were also calculated as 163 participants per group for a 15% effect size and 356 participants per group for a 10% effect size.

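### The primary outcome gives no place to death before day 10, so read literally an early death without recorded S-AGI counts as successful prevention

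*Protocol article*

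**What the plan says.** The Primary outcome section sets the endpoint: "The primary outcome is the 10-day incidence rate of S-AGI". The event is then defined: "The occurrence of S-AGI is defined as the development of gastrointestinal symptoms in a patient who had no symptoms at baseline". A second condition concerns the grade that is recorded: "with an AGI grade of 1 to 4 at the time of assessment". Death is not part of the definition.

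The Secondary outcomes section gives the grading times: "At baseline and on days 4, 8, and 10, AGI grading will be assessed". A patient who dies before day 4 therefore has no post-baseline grade. Death appears only as separate day-7 and day-28 mortality outcomes.

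The Statistical analysis section compares categorical outcomes by chi-squared test. The Discussion fixes the analysis set: "We will use an intention-to-treat approach to include data from all participants regardless of study completion". It adds that the reasons for and numbers of missing data will be reported by group.

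The Sample size section assumes 70% vs 50%, arrives at 94 per group and rounds up: "To account for potential loss to follow-up, we plan to include a total of 200 sepsis patients". That is 100 per group, a 6% allowance.

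On mortality, Background and rationale cites hospital figures of 17% for sepsis and 26% for severe sepsis, and says that in China "the case fatality rate for sepsis-3 is estimated to exceed 30" percent. It also reports that the team's own retrospective cohort "demonstrated a 54% reduction in 28-day mortality among patients who received EA", and then calls the evidence on mortality inconsistent.

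**The concern.** The trial enrols sepsis patients expected to need at least 72 hours of invasive ventilation, so some will probably die before day 10. A patient who dies ungraded cannot meet the event definition, but intention-to-treat keeps that patient in the denominator. Together these make early death score as S-AGI avoided. Removing such patients would conflict with the intention-to-treat commitment.

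Death could also differ between arms, and then the S-AGI proportion mixes prevention with survival. The serious case is an EA arm with more early deaths: it would show fewer S-AGI events even if EA prevented none. This follows from how the endpoint is defined and is more than an analysis detail.

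**Working it through.** **The plan's own figure.** Two-sided α = 0.05, power 0.80, pooled variance, 0.70 vs 0.50 (mean 0.60):

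n = [1.96·√(2·0.6·0.4) + 0.8416·√(0.7·0.3 + 0.5·0.5)]² / 0.20² = (1.3579 + 0.5708)² / 0.04 = 93.0

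The article states 94, which is within rounding. The same formula gives its 163 (70% vs 55%) and 356 (70% vs 60%). Summing binomial probabilities over all tables, the chi-squared test has 80.0% power at 94 per arm and 83.2% at 100. The allowance is 1 − 94/100 = 6%.

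**Model.** Let d be the share of an arm that dies before day 10 without recorded S-AGI. The documents do not give d, so every value below is an assumption. A second assumption is that 70% and 50% apply to the remaining patients. With such deaths counted as S-AGI-free:

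- control rate = 0.70·(1 − d_C)
- EA rate = 0.50·(1 − d_E)
- difference = 0.20 − 0.70·d_C + 0.50·d_E

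**Equal d in both arms, 100 per arm, exact chi-squared power:**

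| d | Control | EA | Difference (points) | Power |
|---|---|---|---|---|
| 0% | 70.0% | 50.0% | 20.0 | 83% |
| 3% | 67.9% | 48.5% | 19.4 | 81% |
| 5% | 66.5% | 47.5% | 19.0 | 79% |
| 10% | 63.0% | 45.0% | 18.0 | 74% |
| 15% | 59.5% | 42.5% | 17.0 | 69% |

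**Direction when d differs.** Lower d in the EA arm shrinks the difference further. Higher d in the EA arm moves it in EA's favour, and it passes the true 20 points once 0.50·d_E > 0.70·d_C, that is d_E > 1.4·d_C. With d = 10% control and 20% EA it is 63% vs 40%, or 23 points.

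**No S-AGI effect (70% in both arms' remaining patients), d = 10% control and 20% EA.** The rates become 0.70·0.90 = 63% and 0.70·0.80 = 56%, a spurious 7-point benefit. The nominal 5% test rejects 17.6% of the time, 17.4% in EA's favour. Counting death as an event gives 63 + 10 = 73% vs 56 + 20 = 76%. That test rejects 7.6% of the time, only 0.7% in EA's favour.

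**S-AGI or death with equal d and a true effect.** At d = 15%: 74.5% vs 57.5%, power 72%, against 69% for S-AGI alone. At d = 10%: 73% vs 55%, 76% against 74%.

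**If deaths were dropped instead,** and were independent of S-AGI risk, the 20-point difference would stand. Power would fall to about 79% with 90 per arm (normal approximation).

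**The case against.** The strongest reply is that the article is silent, and silence in a condensed article is not an error. It nowhere says that an early death counts as S-AGI-free or drops out, and an unseen analysis plan may hold the rule. That stands as a limit on the wording: non-event is the literal result of the event definition plus intention-to-treat, not a stated rule. It does not remove the point, because what counts as the primary event is fixed here, and death has no place in it.

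Other parts also stand:

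- The share d is assumed. S-AGI counts from grade 1 and is expected in 70% of controls, so many patients who die early may already be events. At d = 3% in both arms power is 80.6%, still above the target.
- The 70% comes from clinical observation. If it is a crude rate among all patients, early deaths are already in its denominator and the model discounts twice.
- The cited mortality figures have no day-10 horizon.
- Day-7 and day-28 mortality are reported separately, so a large imbalance would be visible. It would not correct the primary test.
- The stated objective is prevention of S-AGI, and a composite with death changes that question.

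A reader might combine the fatality above 30% with the 54% reduction and infer that EA is expected to save lives, so that the trial loses much of its power. Taking 30% vs 14% 28-day mortality, with a quarter to a half of those deaths early and S-AGI-free (7.5% vs 3.5%, up to 15% vs 7%), power would be 67% down to 47%. The documents do not support that reading. The 54% comes from a retrospective cohort on S-AGI, whereas this trial enrols patients without it. The article calls the mortality findings inconsistent, the sample size assumes no mortality effect, and the early share is not given.

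**Conclusion.** The point holds in a limited form. As written, the endpoint lets death before day 10 without recorded S-AGI score as prevention, in a population for which the article cites mortality of 17% to over 30%.

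A reader might infer that the flaw always dilutes a real effect. It does not: equal or lower EA mortality dilutes, higher EA mortality favours EA, and dropping deaths that are independent of S-AGI risk costs only power.

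With equal early mortality the loss is modest, from 83% to between 81% and 69% for shares of 3% to 15%. It rests on two assumptions: the share itself, and 70% vs 50% applying to the other patients. The more serious risk is a false claim of prevention when EA mortality is higher: 17.6% rejection instead of 5% in the example above. The calculation of 94 per group is not in question.

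**What to change.** 1. Under Primary outcome, state that death before day 10 without recorded S-AGI is not counted as prevention.
2. Pre-specify an analysis of S-AGI or death by day 10. It can be the primary analysis, or a key supporting analysis that must agree before prevention is claimed. Choose before any data are seen by arm.
3. Add a competing-risk cumulative incidence of S-AGI, with death as the competing event, and report S-AGI and death before day 10 separately by arm.
4. Under Sample size, state that the 6% allowance covers loss to follow-up and not deaths, and give the early-death share assumed.

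The cost is a few sentences and one table; mortality is already collected. The composite has a downside: it includes deaths unrelated to the gut and gains little power if mortality is equal (72% vs 69% at 15% in both arms). Its main value is to stop rewarding early death. If agreement of both analyses is required, joint power cannot exceed the smaller of the two.
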